### Intervention

#### e-registration and mHealth

In the intervention areas, the pregnant mothers will be registered in the FWA e-Register database so that they can be tracked and their schedules can be maintained electronically. The FWAs will visit the pregnant mothers’ homes of their designated unions and register them in the eMIS database using an android tablet computer. eMIS software will be used in the android tablet computer to capture the data. Both online and offline data input can be done and the offline data will be automatically synced to the central database once going online. The FPIs will perform data quality checks, approval, and monthly aggregation of union-level data to the sub-district levels. The aggregated list will be sent to the midwives. Then the midwives will call and send text messages to the pregnant mothers whose expected delivery dates are nearby and counsel them to conduct their deliveries at the healthcare facility. The midwives will call three times in case of a failure of the first two attempts to reach each participant of the intervention arm. The text messages will be tailored beforehand in Bangla and the midwives will be trained on how to counsel the pregnant mothers on facility delivery. Following e-Registration, the mHealth intervention will be given once to the pregnant mothers of the intervention arm during 28–36 weeks of their pregnancy. We expect to evaluate the combined effect of e-Registration tracking and mHealth counseling through this study.

### Outcome measures

#### Primary outcome

Institutional delivery

Normal vaginal deliveries, cesarean sections and assisted vaginal deliveries (forceps and vacuum deliveries) conducted at any healthcare facility by a medically trained provider/ skilled birth attendant situated at the study sites will be considered as institutional delivery.

Indicator: Proportion of institutional delivery

Denominator: Total deliveries (A sum of normal vaginal deliveries, cesarean sections and assisted vaginal deliveries)

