## Hypothesis

We hypothesize that e-registration and mHealth will increase institutional deliveries in the hazard-prone areas of Southern Bangladesh.

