### Exclusion criteria

Pregnant mothers with severe pregnancy-related complications at the baseline,Pregnant mothers who will develop severe pregnancy-related complications, migrate out, lost to follow-up, or die during the study period,Mothers who will deliver beyond 42 weeks of their gestational period,Pregnant mothers who will refuse to participate in the study.

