### Sample size

We have planned to recruit and then follow up a minimum of 268 pregnant mothers in the intervention areas and 268 pregnant mothers in the control areas. According to a study conducted in Ethiopia, the implementation of mHealth services using both voice calls and text messages increased facility delivery by 14.7% in the intervention group compared to the control group (43.1% compared to 28.4%; AOR: 1.98 (95%CI: 1.53, 2.55)) [4]. We decided on this proportion we need to determine the number of respondents for our study at a 5% level of error margin and 80% power. Using the formula below we determined the sample size to be 268 for each of the intervention and control groups.

$$n=\frac{p_{1}(100-p_{1})+p_{2}(100-p_{2})}{{\left(p_{1}-p_{2}\right)}^{2}}x{\left(z_{\alpha }+z_{\beta }\right)}^{2}x\;g$$

-----------------------------------------

Here,

p_1_ = 53.8% (Proportion of institutional delivery in Bangladesh) [19]

p_2_ = 68.5% (Proportion of institutional delivery following intervention assuming a 14.7% increase) [4]

z_α_ = 1.96 (at 5% error margin)

z_β_ = 0.85 (at 80% power)

g = 1.50 (design effect)

non-response rate = 5%

-----------------------------------------

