**Fig 3 pone.0271364.g003:**
[figure not shown]
Conceptual framework of data collection process.

The questionnaire is subdivided into three main sections–screening measure, baseline survey, and end-line survey. During the baseline period, we will screen pregnant mothers using the screening tools. The screening tools will include mothers who will give consent and exclude pregnant mothers with severe pregnancy-related complications, such as eclampsia, antepartum hemorrhage, sepsis, and/or COVID-19 infection. The baseline section is designed to collect data of the respondents about the socio-demographic information, pregnancy-related information, such as parity, gravida, months of pregnancy at the first antenatal visit, counseling on facility visit, birth preparedness plan, knowledge on danger signs, location, and outcome of previous pregnancy and existing comorbidities, and other information such as personal belief, social norm, choice of delivery place, health-seeking behavior in general, and the distance between the respondent’s home, and the nearest healthcare facility. It will take approximately 20 minutes to complete the baseline section of the data collection tool. The pregnant mothers will then be followed-up until their delivery. Then their delivery-related data, such as place of delivery, mode of delivery, and the delivery outcome, will be collected at the end line of the study period using the relevant section of the questionnaire, which will take about 10 minutes to fill up.

Since the baseline, the end line data collection will be done at the end of the fourth month of the study period. The baseline and end-line data collections will be done by face-to-face interviews. The questions will be read out to the participants and the data collectors will fill up the questionnaire with the information given by the mothers. The mothers who will have post-dated delivery, develop severe pregnancy-related complications, will be lost to follow-up, or die during the study period will be excluded from the study. We will exclude post-dated deliveries and mothers with severe pregnancy-related complications as, by nature of the emergence, these deliveries are conducted in the healthcare facility and do not depend on the choice of the respondent.

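### The primary outcome counts a facility delivery only within the study sites but puts no limit on place in the denominator, so a facility birth outside the six sub-districts is coded as not institutional

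*Protocol article*

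**What the plan says.** Under Outcome measures, Primary outcome, the protocol article lists vaginal, cesarean and assisted deliveries and states that those "conducted at any healthcare facility by a medically trained provider/ skilled birth attendant situated at the study sites will be considered as institutional delivery". The indicator is a proportion, with "Denominator: Total deliveries (A sum of normal vaginal deliveries, cesarean sections and assisted vaginal deliveries" as its lower part. The numerator carries a location qualifier and the denominator does not.

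Other sections bear on the same point:

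- Inclusion criteria: women are enrolled by residence in one of the six sub-districts.
- Hypothesis: "e-registration and mHealth will increase institutional deliveries in the hazard-prone areas of Southern Bangladesh".
- Intervention: midwives will "counsel them to conduct their deliveries at the healthcare facility". No limit to facilities in the study area is stated.
- Sample size: the control rate is "53.8% (Proportion of institutional delivery in Bangladesh") and the intervention rate is "68.5% (Proportion of institutional delivery following intervention assuming a 14.7% increase"). The first is a national figure with no site limit.
- Data collection process: "place of delivery, mode of delivery, and the delivery outcome, will be collected at the end line of the study period".
- Exclusion criteria: women who develop severe pregnancy-related complications are excluded, as are those who "migrate out, lost to follow-up, or die during the study period". What counts as migrating out is not defined.

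**The concern.** The trial asks whether registration and counselling bring women to deliver in a facility. Under the stated definition, a woman who follows the advice but uses a hospital outside the study sub-districts leaves the numerator and stays in the denominator. She scores the same as a woman who delivered at home.

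Two consequences follow. If out-of-area delivery is equally common in both arms, both rates and their difference shrink and power falls. If it is not, the gap enters the effect estimate directly. Each arm is a single district (Chandpur for intervention, Bhola for control), so arm and district coincide, and the random intercept for union in the analysis plan cannot separate a district-wide difference in coding from an intervention effect. The package could also be credited for a move that is not a gain: the counselling midwives are employed at facilities in the three intervention sub-districts, and a woman who switches from an outside hospital to one of these would count as a new institutional delivery.

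**Working it through.** **1. Does the wording produce this coding?** The site qualifier can attach to the facility or to the attendant. A hospital outside the six sub-districts, staffed by its own attendants, fails on either reading. The denominator is defined by mode alone, so that delivery stays in it. No section reclassifies it. Three parts of the protocol point to the unrestricted concept: enrolment by residence, counselling for facility delivery without a site limit, and the national rate used as p1.

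**2. The plan's own sample size.** Inputs from Sample size: p1 = 53.8, p2 = 68.5, z values 1.96 and 0.85, design effect 1.50, non-response 5%.

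- 53.8 × 46.2 + 68.5 × 31.5 = 2485.56 + 2157.75 = 4643.31
- 4643.31 / 14.7² = 4643.31 / 216.09 = 21.49
- 21.49 × (1.96 + 0.85)² = 21.49 × 7.896 = 169.7
- 169.7 × 1.5 = 254.5; 254.5 / 0.95 = 267.9, rounded up to 268

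The stated 268 per arm is reproduced and is not in dispute.

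**3. Baseline power.** The effective number per arm is 268 × 0.95 / 1.5 = 169.7. A two-proportion test with pooled variance under the null gives 79.6% power for 53.8% v 68.5%.

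**4. Equal out-of-area share m (assumed).** Recorded rates are 0.538 × (1 − m) and 0.685 × (1 − m), so the difference is 14.7 × (1 − m) points.

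| m, both arms | Control | Intervention | Difference (points) | Power |
|---|---|---|---|---|
| 0% | 53.8% | 68.5% | 14.7 | 79.6% |
| 5% | 51.1% | 65.1% | 14.0 | 74% |
| 10% | 48.4% | 61.7% | 13.2 | 69% |
| 20% | 43.0% | 54.8% | 11.8 | 58% |

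**5. Unequal shares (assumed), planned effect true.**

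- 5% control, 10% intervention: 0.685 × 0.90 − 0.538 × 0.95 = 0.6165 − 0.5111 = 10.5 points, power 50%.
- 10% control, 5% intervention: 0.685 × 0.95 − 0.538 × 0.90 = 0.6508 − 0.4842 = 16.7 points, power 88%. The higher figure is not a gain, because the estimate is inflated.

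**6. Unequal shares (assumed), no true effect, 53.8% in both arms.**

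- 10% control, 3% intervention: 0.538 × (0.97 − 0.90) = +3.8 points, 26% of the planned 14.7.
- 15% control, 5% intervention: 0.538 × (0.95 − 0.85) = +5.4 points, 37% of 14.7.
- Reversing either pattern reverses the sign.

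These figures take the design effect of 1.50 as given and use a simple comparison of proportions, not the adjusted mixed model. They show scale and are not forecasts.

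**The case against.** The wording may simply be loose. The sentence begins with any healthcare facility, the qualifier follows the attendant, and the denominator does not say that it includes births wherever they occur. A site limit could even be deliberate, since the hypothesis speaks of deliveries in the hazard-prone areas. These points justify asking the investigators what they meant, but they do not rescue the definition. The secondary objectives attach the geography to the mothers, and a literal coder would still score an outside hospital birth as a failure.

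Three stronger readings are tempting, and the documents do not support them:

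- *That misclassification does differ by arm.* No document gives out-of-area shares, and Study design and setting assumes that Bhola resembles Chandpur in location, health care and care-seeking. That similarity is itself an assumption, so a difference is possible but not shown.
- *That any delivery outside a woman's own sub-district is lost.* The sites are all six sub-districts. A Kachua resident who delivers at a facility in Chandpur Sadar is within the study sites and counts. Only facilities outside all six are affected.
- *That every woman who delivers in an outside hospital is scored as a failure.* The severe-complication exclusion removes some referrals. The migration exclusion, read broadly, could remove others. Both reduce the affected group, but neither covers an uncomplicated or planned delivery elsewhere by a woman who has not moved. Using the migration rule for her would exclude her on her place of delivery, which is part of the outcome.

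It is also fair that the coding can be settled before analysis from data already planned. That makes the correction cheap; it does not make the present wording right.

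**Conclusion.** The point holds as a defect in the stated primary outcome. Followed literally, the definition codes an out-of-area facility birth as not institutional for any woman whom the exclusions do not remove, and so measures something other than what the counselling promotes and the sample size assumes.

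The size cannot be derived from the documents. If shares are small and similar, the loss is mild: 0.7 points at 5% in both arms. At 20% in both arms it is 2.9 points, with power about 58%. Bias from unequal shares is conditional on a district difference that is plausible but undocumented; its direction is unknown. The definition should be corrected before outcomes are classified.

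**What to change.** Delete the site qualifier, so that the primary outcome is delivery by a skilled attendant in any healthcare facility, wherever located, among enrolled residents of the six study sub-districts. Apply the rule identically in both arms. State that travelling elsewhere to deliver is not migrating out. Record at end line whether the facility lies inside or outside the study sub-districts, and report that split descriptively by arm.

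If the investigators did intend a site limit, they should justify it and say how outside deliveries are handled, in the same way for both arms.

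The cost is a one-line outcome amendment and the matching registry update. Place of delivery is already collected at end line, and the sample size stays at 268 per arm because the unrestricted definition is the one that 53.8% v 68.5% assumes.

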### Secondary outcome

Mode of delivery

Indicator: Proportion of normal vaginal deliveries

  Proportion of cesarean sections

  Proportion of forceps and vacuum deliveries

Denominator: Total deliveries

2. Birth outcome

Indicator: Proportion of live births

  Proportion of stillbirths

Denominator: Total births

### Data management and analysis plan

We will analyze the data in R 4.1.2. We will do a frequency distribution and proportion analysis for categorical variables, and for continuous variables, we will perform a mean and standard deviation analysis. We will use chi-square test to make comparison between the groups. Finally, a random-intercept mixed-effect logistic regression model will be fitted to explain the relationship of e-Registration and mHealth package with institutional delivery, where the union will be included as the random intercept. An adjusted odds ratio with p-value less than 0.05 will be considered statistically significant. 95% confidence interval will be calculated from the logistic regression model.

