### Study design and setting

The study will be an open-label two-arm non-randomized controlled cluster trial for six months where Chandpur Sadar, Kachua, and Faridganj sub-districts will be the intervention arm as MIS unit; DGFP will initiate the eMIS registration system in these three sub-districts of Chandpur district. Chandpur is a district under the Chattogram division, located in the Southern part of Bangladesh, and is a disaster-prone area. There are 14 unions in Chandpur Sadar, 12 in Kachua, and 15 in the Faridganj sub-districts of Chandpur [18]. The Government of Bangladesh has taken the initiative to implement various models in different districts, such as the Maternal, Newborn, and Child Survival (MNCS) and Maternal, Newborn and Child Health (MNCH) project by UNICEF; Maternal, Newborn Health Initiative (MNHI) through joint UN initiatives; and USAID supported program MaMoni. But none has chosen Chandpur district as their project implementation site. Again, the majority of the social and health indicators of Chandpur Sadar, Faridganj, and Kachua sub-districts are below national estimates mostly due to the hazard-prone nature of these areas [18]. So, we have chosen these three sub-districts of Chandpur district as intervention areas. The e-registration and mHealth services are not available in Bhola District. In addition, Bhola is likely to be similar to Chandpur, especially in terms of its geographical location, susceptibility to disasters, and health care and care-seeking practices of the inhabitants [18]. So, we have selected the Bhola Sadar, Charfesson, and Lalmohan sub-districts of the Bhola district as the control arm. Bhola Sadar has 13 unions, Charfesson has 14 unions, and Lalmohan has 9 unions [19]. Unions will be considered as cluster units, and individual study participants will be the sample unit.

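### The chi-square comparison of groups ignores clustering by union, and it is the only stated test that could apply to between-arm comparisons of mode of delivery and birth outcome

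*Protocol article*

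**What the plan says.** Under Data management and analysis plan, after the descriptive summaries, the protocol article states: "We will use chi-square test to make comparison between the groups". It does not say which variables the test covers and mentions no adjustment for clustering.

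It then introduces a random-intercept mixed-effect logistic regression to "explain the relationship of e-Registration and mHealth package with institutional delivery, where the union will be included as the random intercept". Statistical significance is defined only for the adjusted odds ratio, and the 95% confidence interval is taken from the logistic model.

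Two other sections treat the data as clustered. Study design and setting says "Unions will be considered as cluster units, and individual study participants will be the sample unit". Sample size lists "g = 1.50 (design effect" among its inputs.

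Secondary outcome lists the proportions by mode of delivery (for example "Proportion of cesarean sections") and the proportions of live births and stillbirths. No test or model is named for them. The Objectives section words the secondary aims as determining prevalence, modes of delivery and birth outcomes.

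**The concern.** An ordinary chi-square test treats every woman as an independent observation. Here arm is constant within a union, because the arms are separate sub-districts in two different districts. Variation between unions therefore enters the variance of every between-arm comparison, and the ordinary test leaves it out. For any positive ICC its p-values are too small.

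The plan recognises this when it sizes the trial and when it models institutional delivery, but not in the sentence that compares the groups. At stake is a spurious between-arm difference in, say, caesarean sections or stillbirths, in a study whose Discussion says its evidence may help the government decide on roll-out.

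**Working it through.** **Inputs from the protocol article**
- Sample size: proportions 53.8% and 68.5%; "z_α_ = 1.96 (at 5% error margin"); "z_β_ = 0.85 (at 80% power"); design effect 1.50; non-response 5%; 268 women per arm.
- Study design and setting: 14 + 12 + 15 = 41 intervention unions and 13 + 14 + 9 = 36 control unions, 77 in all.

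**Step 1. Reproduce the stated sample size.**
- Variance term: 53.8 × 46.2 + 68.5 × 31.5 = 2485.56 + 2157.75 = 4643.31.
- Divide by 14.7² = 216.09 and multiply by (1.96 + 0.85)² = 7.8961: 169.67.
- Multiply by 1.5: 254.5. Divide by 0.95: 267.9, so 268.

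The stated figure reproduces only with the 1.5 included, so 1.5 is the plan's working assumption about clustering.

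**Step 2. True level of the unadjusted test at that design effect.** With design effect g, the 1-df chi-square statistic (one proportion compared between two arms) is inflated on average by g. The true two-sided level is 2 × (1 − Φ(1.96/√g)).
- g = 1.5: 1.96/1.2247 = 1.600, which gives 0.110.
- To hold 5%, the unadjusted statistic would have to exceed 3.84 × 1.5 = 5.76, that is, an unadjusted p below about 0.016.

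**Step 3. Translate g into an ICC.** If all 77 unions contribute, the mean is 536/77 = 6.96 women per union. With g = 1 + (6.96 − 1) × ICC, g = 1.5 corresponds to ICC = 0.5/5.96 = 0.084.

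**Step 4. Range for the secondary outcomes.** The document gives no ICC for mode of delivery or birth outcome, so the values below are assumptions.

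| Assumed ICC | g | True level of nominal 5% test |
|---|---|---|
| 0.01 | 1.06 | 5.7% |
| 0.02 | 1.12 | 6.4% |
| 0.05 | 1.30 | 8.5% |
| 0.10 | 1.60 | 12.1% |

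**Step 5. Check by simulation.** Beta-binomial data with no arm effect were generated for 41 and 36 unions of near-equal size, 268 women per arm, with 20,000 replicates. At ICC 0.084 the ordinary chi-square test rejected in 10.6%, 11.1% and 10.8% of replicates for outcome proportions of 0.538, 0.33 and 0.03. At ICC 0.02 it rejected in 6.5% to 6.9%. This agrees with the formula.

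**The case against.** The strongest reply is that the chi-square sentence names no outcome. It sits between the descriptive summaries and the final model, which fits a preliminary bivariate step. The secondary objectives are worded descriptively, the only hypothesis concerns institutional delivery, and the significance rule is attached only to the adjusted odds ratio. If the secondary outcomes are simply reported as proportions, no error rate arises. This stands as a limit: use of the test for those outcomes is inferred from the absence of any other method, so the 11% is conditional.

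It can also be said that 1.50 was set for institutional delivery and may not carry over to caesarean section or stillbirth. That stands too. At an ICC of 0.01 the inflation is small.

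A third reply is that an analysis plan not shown may specify an adjusted test. That does not remove the point. The article names a test that in its usual form assumes independence, and this conflicts with its own cluster definition and design effect. The objection is to what is stated, not to missing detail.

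A reader might infer more than the document supports:
- That the primary result is compromised. It is not, because institutional delivery has the union random-intercept model and the adjusted odds ratio governs. A chi-square p-value for it would be preliminary, and disagreement with the model would change no decision.
- That the reported confidence intervals will be too narrow. The only intervals planned come from the clustered model.
- That the secondary outcomes certainly carry double the nominal error. Neither the use of the test for them nor their ICC is stated.
- That tests in a baseline table are an error here. How to present baseline balance is a reporting preference and is not part of this point.

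**Conclusion.** The concern holds in conditional form. As written, the chi-square comparison is inconsistent with the plan's own treatment of unions as clusters, and any between-arm p-value it produces for mode of delivery or birth outcome will be too small whenever the ICC is positive. On the plan's own design effect the excess is about 6 percentage points (11% against 5%). Over the assumed ICCs it runs from under 1 to about 7 points.

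This rests on three assumptions: that the test is used for the secondary outcomes, that union is the right level of clustering (as the plan takes it to be), and that all 77 unions contribute in roughly equal numbers. With fewer contributing unions there are more women per union, and the same ICC gives a larger inflation. The matter should be corrected, but it does not threaten the main conclusion.

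**What to change.** State which variables the chi-square test covers. For every between-arm comparison of an outcome, replace the unadjusted test with the union random-intercept logistic model already planned for institutional delivery.

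That model may be unstable for rare outcomes such as stillbirth and assisted delivery: at an assumed 3% event rate there would be about 268 × 0.03 = 8 events per arm. For these, name a cluster-adjusted chi-square test (Rao-Scott or Donner).

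If the secondary outcomes are meant to be descriptive, say so and report the proportions with cluster-robust intervals and no unadjusted p-values.

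The change takes a few sentences and needs no extra participants or data. It can be done in R, the planned software. The downside is slightly larger p-values and, for the rare outcomes, a second method to specify.

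### If mode of delivery and birth outcome are compared between the two non-randomised districts, the only method the plan supplies is a chi-square test that neither adjusts for baseline differences nor allows for clustering by union

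*Protocol article*

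**What the plan says.** The protocol article, under Study design and setting, describes the design: "The study will be an open-label two-arm non-randomized controlled cluster trial for six months". Three sub-districts of Chandpur form the intervention arm and three of Bhola the control arm. The case for comparability is that "Bhola is likely to be similar to Chandpur, especially in terms of its geographical location", along with disaster risk and care-seeking. On clustering the same section says: "Unions will be considered as cluster units, and individual study participants will be the sample unit".

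The secondary outcomes are mode of delivery (with indicators such as "Proportion of cesarean sections") and birth outcome (live birth, stillbirth). Each is defined by an indicator and a denominator, and neither is tied to a test.

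The Data management and analysis plan gives two between-group methods. The first is "We will use chi-square test to make comparison between the groups", with no variable or outcome named. The second is introduced as the final step: "a random-intercept mixed-effect logistic regression model will be fitted to explain the relationship of e-Registration and mHealth package with institutional delivery", with union as the random intercept and an adjusted odds ratio judged at p below 0.05.

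Under Data collection process, the baseline questionnaire covers socio-demographic items, parity, gravida, distance to the nearest facility, and "location, and outcome of previous pregnancy and existing comorbidities".

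**The concern.** By asking for an adjusted odds ratio and a union random intercept for institutional delivery, the plan accepts that a crude comparison of these two districts is not enough. The same reasoning applies to other outcomes measured in the same women. Caesarean delivery and stillbirth plausibly depend on parity, comorbidity, obstetric history and distance to a facility, and any of these may differ between Chandpur and Bhola.

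If an analyst compares the secondary outcomes using only the methods in the article, the chi-square is what remains. It yields no effect estimate, uses none of the baseline data, and treats women from the same union as independent. Confounding and clustering are separate faults: the first moves the estimate, the second understates its uncertainty. A significant caesarean difference could then appear beside an adjusted primary result although the package had changed nothing, or a real difference could be hidden.

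**Working it through.** **The plan's own figure.** From the Sample size section: p1 = 53.8%, p2 = 68.5%, z values 1.96 and 0.85, design effect 1.50, non-response 5%.

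- [0.538 × 0.462 + 0.685 × 0.315] / 0.147² × (1.96 + 0.85)² = 169.7
- 169.7 × 1.5 = 254.5
- 254.5 / 0.95 = 267.9, rounded up to 268 per arm

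The 268 reproduces. It concerns institutional delivery only, so it neither supports nor weakens this point. It does show that the plan expects clustering to matter.

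**Clustering alone.** If the true variance is 1.5 times what the chi-square assumes and there is no difference between districts, the error rate is 2 × [1 − Φ(1.96 / √1.5)] = 2 × [1 − Φ(1.600)] ≈ 11%, not 5%. This borrows the design effect of 1.50 from the primary outcome. No value is given for the secondary outcomes.

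**Confounding alone.** The article gives no caesarean or stillbirth rate, so every rate below is an assumption. I take 255 analysed per arm (268 × 0.95 = 254.6), no package effect, and clustering set aside. The rejection probability at 0.05 comes from the non-central chi-square on 1 df, with p̄ the mean of the two proportions and

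ncp = (p1 − p2)² / [2 p̄(1 − p̄) / 255]

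| Pre-existing caesarean proportions | ncp | Rejection rate |
|---|---|---|
| 30% v 35% | 1.45 | 0.226 |
| 30% v 40% | 5.60 | 0.658 |

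Dividing the second ncp by 1.5, as a test corrected for clustering would, gives 3.74 and a rejection rate of about 0.49. Correcting for clustering does not cure the bias.

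**How a measured baseline factor could create such a gap.**

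- Strong factor (risk 20% without it, 50% with it; odds ratio 4), held by 40% v 60% of women: 0.4 × 0.5 + 0.6 × 0.2 = 0.32, against 0.6 × 0.5 + 0.4 × 0.2 = 0.38. Crude odds ratio 1.30, rejection rate 0.295.
- The same factor held by 35% v 65%: 0.305 v 0.395. Crude odds ratio 1.49, rejection rate 0.568.
- Milder factor held by 30% v 50%, risk 20% without it. With odds ratio 2 (risk 33.3% with it): 24.0% v 26.7%, crude odds ratio 1.15. With odds ratio 3 (risk 42.9% with it): 26.9% v 31.4%, crude odds ratio 1.25.

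So the spurious crude odds ratio runs from about 1.15 to 1.49 over these assumptions.

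**Sparse outcomes.** At an assumed stillbirth risk of 1% to 3%, 268 × 0.01 to 268 × 0.03 gives about 3 to 8 stillbirths per arm. That is too few for a covariate-adjusted model to be dependable.

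**The case against.** The strongest reply is that the plan never says it will do this. A reader might infer that mode of delivery and birth outcome are to be tested by chi-square and the result credited to the package. The document does not support that reading. The chi-square sentence names no outcome. It sits between the descriptive statistics and the final model, so it could equally mean baseline characteristics or a crude look at the primary outcome. The Objectives section speaks of an effect for institutional delivery only and words the secondary objectives descriptively. The Hypothesis concerns institutional delivery alone. The significance rule is attached to the adjusted odds ratio, not to the chi-square. All of this stands, and it makes the point conditional.

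A second reply is that an article may leave the analysis of secondary outcomes to a fuller document that is not shown. Silence would indeed be no finding. Here, however, the text does give a method for comparing the groups, leaves its scope open, and restricts the better method to one outcome. Any fuller plan would still have to be reconciled with that wording.

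A third reply is that the rates are invented and that adjustment is no full remedy. Both are correct. The calculations show how the test would behave if a gap existed, not that one does. With one district per arm, women's covariates cannot remove district-level differences such as the supply of facilities. That calls for cautious wording of results. It does not justify leaving measured differences and union clustering unaddressed.

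**Conclusion.** The point holds in conditional form. If the secondary outcomes are compared between arms, the only method the article supplies is unadjusted and ignores union clustering, and differences between the women could be read as package effects. Under the stated assumptions the rejection rate with no package effect is about 23% for a 30% v 35% pre-existing gap and about 66% for 30% v 40%. Ignoring a design effect of 1.5 alone gives about 11%. The caesarean rates are assumed, and the true gap between the districts is unknown.

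The document does not establish that the sponsor intends to claim a package effect on these outcomes. The primary analysis and the sample size are not affected. The change is worth making because the better method is already in the plan, the covariates are already collected, and the cost is small.

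**What to change.** In the Data management and analysis plan:

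1. Limit the chi-square test to describing baseline characteristics.
2. For caesarean v other delivery, fit the same union random-intercept logistic model as for institutional delivery, with prespecified baseline covariates from the questionnaire (such as parity, comorbidities, outcome of previous pregnancy, distance to facility and socio-demographic items). Report the adjusted odds ratio with its 95% confidence interval.
3. For stillbirth and forceps/vacuum delivery, report proportions by arm with confidence intervals that allow for clustering by union, and draw no between-arm conclusion.
4. State that adjusting for women's covariates does not remove differences between the districts themselves.

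The cost is a few sentences and a few more model fits on data already collected, with no extra participants or visits. The downside is somewhat wider intervals for caesarean delivery and no inferential statement on the rare outcomes.
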